## Aim

The aim of this national multi-center study performed by Genomic Medicine Sweden (GMS), in close collaboration with the Clinical Genomics Platform at Science for Life Laboratory (SciLifeLab), is to evaluate whether application of WGS and WTS combined, collectively termed WGTS, is technically feasible and can be implemented as an efficient clinical tool with a high diagnostic accuracy in patients with ALL and AML. Specifically, the combined workflow of WGTS will be compared with current SoC methodologies to identify potential benefits and challenges of WGTS implementation in a routine diagnostic setting. This study will also address whether WGTS will improve the diagnostic yield and patient management as well as if these assays combined are cost-effective. The ultimate goal of this study is to evaluate if WGTS can replace current diagnostic SoC methods of patients with ALL and AML across Sweden. This manuscript outlines the conceptual and experimental designs for the study.

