### Endpoints

Primary and secondary endpoints are listed in Table 1.

**TABLE 1 T1:** Primary and secondary endpoints.

Primary study endpoint (key phases)	Primary outcome measure
Diagnostic efficiency (retrospective and prospective phases)	Percentage of acute leukemia patients for whom all mandatory and highly recommended genetic variants found by SoC methods are also detected by WGTS*
Improved diagnostic yield (retrospective and prospective phases)	Percentage of acute leukemia patients for whom genetic variants relevant for classification or risk stratification are identified by WGTS* but not by SoC
**Secondary study endpoints (key phases)**	**Secondary outcome measure**
Technical feasibility (retrospective and prospective phases)	Percentage of patients for whom WGTS* analysis and interpretation is successful
Clinical feasibility for routine implementation (real-time validation phase)	Percentage of patients for whom WGTS analysis and interpretation is successful within a given time frame
Clinical utility (prospective and real-time validation phases)	Percentage of acute leukemia patients for whom patient management and/or therapy decision is/could be changed based on variants detected only by WGTS
Health-economic efficiency (all phases)	Micro-costing and cost effectiveness analysis of WGTS* compared to SoC

**For the retrospective phase, only WGS data are available.*

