##### Clinical Utility

Clinical utility is measured by the percentage of patients for whom patient management or therapy decisions (according to national care programs and/or clinical trial protocols) are/potentially could be changed based on variants detected by WGTS, but not SoC diagnostics. Specifically, the percentage of patients for whom WGTS findings lead to targeted treatment options and/or a change in treatment options not identified by SoC will be recorded. This information will be retrieved from registries and retrospective analysis of medical records (prospective and real-time validation phases).

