### WGTS Study Report

During the prospective and real time validation phases, we will prepare a WGTS study report for each patient with the following information:

•Availability of materials for SoC and WGTS.•Sequencing metrics (sequence depth, sequence coverage, and other QC data).•Mandatory and highly recommended variants identified by both SoC and WGTS.•Mandatory and highly recommended variants that are identified by WGTS but not SoC, and if available results of verification experiments.•Mandatory and highly recommended variants that are identified by SoC but not WGTS, and if available results of verification experiments.•Potential impact of WGTS findings on classification, risk stratification and therapy selection.•For the real-time validation phase, turnaround time in calendar days from sample collection to first clinical report (based on tumor-only analysis) and to the final report (tumor/normal analysis).

During the real-time validation phase, in addition to a WGTS study report, we will include WGTS findings in the clinical report according to the standard clinical reporting practice. Also, national review meetings, including physicians, clinical scientists, and bioinformaticians will be held on a regular basis to discuss the findings and their clinical interpretation (in particular, if WGTS detects clinically relevant genomic variants not identified by SoC or if WGTS and SoC show conflicting results) and to harmonize the reports between sites.

We have also prepared standardized templates for collection of metadata (e.g., sample data, sequencing protocol, sequencing platform, genome version, software and parameters used for variant calling, annotation and interpretation, etc.) to ensure that all sites collect the same information.

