### Health-Economics Analysis

The micro-costing analysis will be performed initially at two sites and ultimately at all four sites where WGTS is carried out (Gothenburg, Lund, Stockholm, and Uppsala). A generic micro-costing spreadsheet will be developed and applied to Swedish genetic laboratories estimating the average cost of SoC and WGTS. The micro-costing will capture the economic burden to each laboratory; including the costs of personnel, equipment/material, bioinformatic analysis and interpretation, storage and compute costs, test consumables as well as platforms used (for WGTS) and potentially iterative testing. An activity-based costing model will be applied to calculate the total cost of the included diagnostic techniques. The analysis will take into account that some rapid conventional testing will be required in parallel to WGTS.

Cost-effectiveness of WGTS in comparison with SoC will be estimated using economic simulation modeling where the value of WGTS in quality adjusted life years is driven by the proportion of patients for whom management or therapy decision is/could be changed based on variants detected by WGTS, but not by SoC diagnostics. The outcome of patients where WGTS led to changes in risk stratification will be compared to the outcome of patients in risk groups defined by SoC only.

Based on literature, study outcomes (i.e., improved diagnostic yield and clinical utility), and registry data (e.g., the Swedish Blood Cancer Register, the National Patient Register, and the Swedish Prescribed Drug Register from the National Board of Health and Welfare), a simulation model will be built to estimate the diagnostic and the long-term cost for AML and ALL patients. The model will also be able to estimate the long-term health outcomes and the incremental cost effectiveness ratio of WGTS vs. SoC.

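### Clinical utility and the QALY driver count what WGTS adds to SoC but have no term for what would be lost if WGTS replaced SoC

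*Protocol article*

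**What the plan says.** The Aim section sets the decision to be informed: "The ultimate goal of this study is to evaluate if WGTS can replace current diagnostic SoC methods".

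Table 1 (Endpoints) measures clinical utility as the percentage of patients for whom "patient management and/or therapy decision is/could be changed based on variants detected only by WGTS". The Clinical Utility section has the same direction: decisions that "are/potentially could be changed based on variants detected by WGTS, but not SoC diagnostics".

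Health-Economics Analysis carries this into the model in three places:
- QALY value depends on the share of patients whose treatment plan "is/could be changed based on variants detected by WGTS, but not by SoC diagnostics".
- The inputs taken from the study itself are given as "study outcomes (i.e., improved diagnostic yield and clinical utility", and the list closes there. Literature and registry data are the other sources.
- "The outcome of patients where WGTS led to changes in risk stratification will be compared" with the outcome of patients in risk groups defined by SoC alone.

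On the cost side, the same section compares WGTS with SoC and allows for some rapid conventional tests that continue alongside WGTS.

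The WGTS Study Report lists, for each patient, "Mandatory and highly recommended variants that are identified by SoC but not WGTS", with verification results where available. Its item on impact for classification, risk and therapy refers to WGTS findings only.

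**The concern.** Replacement has two effects on information. Some patients gain a variant that SoC did not show, and some lose a variant that only SoC showed. The utility endpoint and the QALY driver count the first and have no place for the second.

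The effect side of the model therefore describes WGTS added to full SoC, while its cost side describes WGTS plus a few retained rapid tests set against SoC. An incremental cost-effectiveness ratio needs the same strategy in its numerator and its denominator. If the costs are those of replacement and the effects those of an add-on, the ratio favours WGTS, and it would be read as evidence for a national change of diagnostic practice.

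**Working it through.** **1. Figures in the document.** The plan gives no figure for this point, so there is none to reproduce. Two context figures check out. Clinical utility is measured in the prospective and real-time phases, 350 + 100 = 450 patients. The reclassification rate cited in the Discussion is 19/117 = 16.2%, stated as 16%.

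**2. Which measure counts which discordance.**

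| Measure | WGTS-only variant | SoC-only variant | Judges effect on management | Named as model input |
|---|---|---|---|---|
| Diagnostic efficiency (primary) | not in the Table 1 measure | patient is a failure | no | no |
| Sensitivity, specificity (Statistical Analysis) | counts against specificity | counts against sensitivity | no | no |
| Improved diagnostic yield (primary) | counted | not counted | no (classification or risk only) | yes |
| Clinical utility (secondary) | counted | not counted | yes | yes; its proportion is the QALY driver |

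No measure that counts SoC-only variants reaches the model, and no measure that reaches the model counts them.

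**3. What this does to the modelled effect.** Let g be the proportion of patients whose management changes because of a WGTS-only variant. Let l be the proportion with a management-relevant SoC-only variant that the retained rapid tests would not find. Let q_g be the mean QALY effect of such a change and q_l the mean QALY loss from such a miss.
- Driver as written: g × q_g
- Replacement: g × q_g − l × q_l
- Omitted term: l × q_l

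The driver has the same value whatever l is.

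**4. Whether follow-up could supply the omitted term.** The Reporting section keeps SoC as the primary source for subtype classification for the whole study, with WGTS as complementary information. No participant is managed without SoC results, so harm from a WGTS miss cannot appear in observed outcomes. It has to be modelled, and Health-Economics Analysis names no input for it.

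**5. Illustration of how the omission behaves.** All loss rates are assumed, and gains and losses are given equal QALY weight (q_g = q_l). N = 450, net = g − l, factor = g / (g − l). The first gain is the cited 16% (0.16 × 450 = 72 patients credited); the second is an assumed 5% (22.5 patients).

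| l | Patients losing (450 × l) | Net at g = 16% | Factor | Net at g = 5% | Factor |
|---|---|---|---|---|---|
| 1% | 4.5 | 15% | 1.07 | 4% | 1.25 |
| 2% | 9 | 14% | 1.14 | 3% | 1.67 |
| 4% | 18 | 12% | 1.33 | 1% | 5.00 |
| 7% | 31.5 | 9% | 1.78 | −2% | sign reversed |

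In every row the planned driver would still read 16% or 5%.

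**The case against.** The strongest reply is that the debit side exists already. Diagnostic efficiency is the first primary endpoint, and one SoC variant missed by WGTS makes the patient a failure. Sensitivity and specificity are planned. National review meetings discuss conflicting WGTS and SoC results. This stands, and it limits the point. A reader might infer that the whole case for replacement is one-sided; the documents do not support that. What remains is that these measures do not ask whether a miss would change management and are not linked to the model.

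A reader might also infer that WGTS could never lower the modelled health outcome. That is too strong. The driver counts decisions changed, not improved, and the outcome comparison for reclassified patients could go either way, so q_g may be negative. The supportable statement is that WGTS misses cannot lower the outcome through the stated driver.

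It is tempting to take loss rates from the 87% to 96% concordances cited in the Discussion. Those are per variant, from chronic lymphocytic leukemia, and for WGS without WTS. The article attributes many of the discrepancies to alterations outside the targeted panel or to filtered germline calls. For AML it cites concordance with cytogenetics of about 96% for shallow WGS and 99% for WTS. None of these is a patient-level rate of management loss. The 16% gain likewise comes from another study, using tumor-only WGS at 60×.

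Two further replies carry some weight. Clinical utility is openly defined as incremental, so it is not wrong as a measure of added value; the difficulty is its use as the effect term for replacement. And a fuller health-economic plan may exist. But the driver and the closed list of study inputs are stated content, so the objection is to what is written and not to missing detail.

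**Conclusion.** The point holds for clinical utility and cost-effectiveness. The endpoint, the QALY driver and the study inputs to the model are gain-only, while the decision and the cost comparison concern replacement. Followed as written, the plan omits a loss term and so biases this part of the case towards WGTS.

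The direction rests on one assumption: that some patients have a management-relevant SoC-only variant not covered by the retained rapid tests, and that losing it does harm on average. If there are no such patients, there is no bias. The size cannot be estimated from the documents; the factors in the illustration show only how the result depends on assumed values. The accuracy endpoints are unaffected.

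**What to change.** Three linked changes:

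1. **WGTS Study Report.** Extend the impact item to variants found only by SoC, taking account of any verification result, so that a SoC call that is not confirmed is not counted as a loss.
2. **Table 1 and Clinical Utility.** Beside the existing measure, report the percentage of patients whose management would have differed had only WGTS plus the retained rapid tests been available. Show gain and loss separately.
3. **Health-Economics Analysis.** For the replacement scenario, drive the QALY model by both proportions, each with its own QALY effect. Keep the gain-only version, if wanted, as an add-on scenario with add-on costs.

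SoC-only variants are already recorded for each patient and conflicting results already go to national review meetings, so recruitment, sequencing and the primary endpoints do not change. The cost is a small amount of extra adjudication, cheaper if done as the reports are completed than by reopening records later. The utility figure and the cost-effectiveness ratio may become less favourable to WGTS.

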**FIGURE 1 F1:**
[figure not shown]
Overview of the study phases, planned data generation, analysis, and reporting. Results from SoC diagnostics will be collected in parallel for all patients. T, tumor; N, normal; WGS, whole-genome sequencing; WTS, whole-transcriptome sequencing.

The prospective phase encompasses WGTS of prospectively collected samples from approximately 350 adult and pediatric ALL and AML patients (Figure 1). WGS will be performed for tumor (90×) and normal (30×) samples, and WTS (50 million read pairs) for tumor samples only. The choice of sequence depth is based on recent recommendations and data from a previous study including acute leukemia samples (4, 14, 15). Samples will be processed in parallel with SoC methods but without a strict time limit for analysis and interpretation. The duration of this phase will be approximately 12 months, starting in May 2021.

The real-time validation phase comprises WGTS of prospectively collected samples from approximately 100 ALL and AML patients, as described for the prospective phase (Figure 1). The aim is to perform WGTS and report the results within the required time frame for genetic diagnostics of acute leukemias in parallel with SoC methods. The duration of this phase will be 3–6 months.

During the follow-up phase, patient outcome data will be recorded for those included in the prospective and real-time validation phases. At least 2 years of follow-up after the last included patient will be required for meaningful health-economic analysis.

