### Sample Preparation

A bone marrow sample will be used for chromosome banding and FISH analyses. From the same sample, DNA and RNA will be extracted using standard procedures at each participating site. In the event of limited material from a bone marrow sample, peripheral blood may be used. The expected tumor purity in bone marrow as well as peripheral blood samples is >80–90%. WGTS of leukemic samples will be performed using surplus DNA and RNA that remain after SoC tests in most cases, without requiring additional sampling.

As germline material, a skin biopsy will be collected from which fibroblasts are cultured and DNA prepared. Alternatively, T-cells are isolated (adult AML) or a remission sample (taken at day 29) is used (adult ALL) as an alternative source of germline DNA. If a patient does not achieve remission, germline DNA will be extracted from a buccal swab sample also collected at day 29.

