### Reporting

For the whole study duration SoC will be the primary data source for subtype classification and the study data will be regarded as complementary information. Genetic variants of diagnostic, prognostic, and/or predictive impact detected by WGTS will be interpreted and recorded according to the standard procedure at each participating center.

In the real-time validation phase, all mandatory variants detected by WGTS will be included in the first clinical report [after 2 (ALL) or 3 (AML) weeks], whereas highly recommended variants will be included the final clinical report (after 4 weeks), and may potentially influence classification/risk stratification and treatment.

In the prospective phase, clinically relevant variants that are detected by WGTS, but not by SoC, will be reported to the hematologist/pediatric oncologist as a complementary clinical report after being verified with another clinically validated method (e.g., FISH, PCR or NGS-based gene panels). Thus, also in this phase, such variants may influence risk classification and treatment.

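### If reclassified means actually changed by WGTS, the outcome comparison leaves out deaths before the WGTS report and raises that group's apparent survival

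*Protocol article*

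**What the plan says.** The contrast, in which SoC alone determines the comparator's risk groups, is described in the protocol article under Health-Economics Analysis: "The outcome of patients where WGTS led to changes in risk stratification will be compared to the outcome of patients in risk groups defined". The sentence just before it, on what drives quality-adjusted life years in the simulation model, counts changes in management that were made as well as changes that could have been made.

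How soon WGTS can change a risk group depends on the phase.

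- **Prospective phase, about 350 patients.** Study Design states: "Samples will be processed in parallel with SoC methods but without a strict time limit for analysis and interpretation". Under Reporting, a clinically relevant variant found by WGTS but not by SoC goes to the treating physician "as a complementary clinical report after being verified with another clinically validated method". The section then adds: "Thus, also in this phase, such variants may influence risk classification and treatment".
- **Real-time validation phase, about 100 patients.** Reporting gives a first clinical report after 2 or 3 weeks and a final one after 4 weeks. Data Interpretation exempts adult ALL from the 4-week limit, because the remission sample is collected at day 29.
- **Both phases.** Reporting keeps SoC as the primary source for subtype classification throughout. WGTS Study Report promises a report for each patient, and one of its items is: "Potential impact of WGTS findings on classification, risk stratification and therapy selection". Turnaround time is listed there for the real-time phase only.

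The article states no time origin or landmark for this contrast. A condensed article may leave those to the full plan. The point here is the group definition that it does state.

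**The concern.** Under the natural reading, the exposed group is defined by something that happens after diagnosis and takes time. A patient who dies while sequencing, interpretation or verification is still under way can never be someone whose risk group WGTS changed. Everyone in the reclassified group has, by definition, survived the waiting period. The comparison group carries no such guarantee.

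This is separate from confounding by prognosis. It remains even if reclassification carries no prognostic information, and adjusting for risk factors at diagnosis does not remove it. Acute leukemia is a setting where some deaths can be expected early, within a reporting delay of weeks to months. At stake is a survival advantage for reclassified patients that could be read as a benefit of WGTS in the health-economic evaluation.

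**Working it through.** **1. Who is affected.** The article's counts add up: 150 + 100 + 350 + 100 = 700 in total, and 350 + 100 = 450 with outcome follow-up. The phase without a time limit holds 350/450 = 78% of the followed patients.

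**2. Which reading the text supports.** The model-driver sentence, and the Clinical Utility section, include hypothetical changes explicitly. The outcome sentence that follows speaks only of changes that WGTS led to. The authors mark hypothetical changes where they mean them, so an actual change is the more natural reading. The other reading is not excluded.

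**3. Inflation of the reclassified group.** Let S be true 2-year survival, the same in both groups (no WGTS effect), and q the share who die before the report. Both are assumptions; the documents give neither. The reclassified group then shows S/(1 − q), and the artefact is S/(1 − q) − S.

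| S | q = 5% | q = 10% | q = 20% |
|---|---|---|---|
| 50% | 52.6% (+2.6 points) | 55.6% (+5.6) | 62.5% (+12.5) |
| 70% | 73.7% (+3.7) | 77.8% (+7.8) | 87.5% (+17.5) |

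**4. If the early deaths are also counted in the SoC group.** The article does not say this, so the step is conditional. Take 16% with a reclassifying result, the rate (19/117) that the Discussion cites from an earlier study, used only for illustration. With S = 50% and q = 10%, the SoC group shows 0.84 × 0.50 / (0.84 + 0.16 × 0.10) = 0.420/0.856 = 49.1%. The gap becomes 55.6 − 49.1 = 6.5 points instead of 5.6.

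**5. Dependence on report delay.** Same setting as step 4, but q follows from the report time d: q = 1 − S(d). The hazard is constant over the first 2 months and constant at another level afterwards. With 10% dead by 2 months and 2-year survival of 50%:

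| Report at | S(d) | Reclassified | SoC group | Artefact |
|---|---|---|---|---|
| 0.5 month | 0.974 | 51.3% | 49.8% | +1.6 points |
| 1 month | 0.949 | 52.7% | 49.5% | +3.2 |
| 3 months | 0.876 | 57.1% | 48.8% | +8.2 |
| 6 months | 0.809 | 61.8% | 48.2% | +13.6 |

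Artefacts are taken from unrounded values. Varying early death from 3% to 20% gives +0.5 to +6.9 points for a report at 0.5 to 1 month and +3.7 to +20.5 points at 3 to 6 months. With 2-year survival of 80% and early death of 3% to 10%, the range over all four report times is +0.7 to +12.6 points. The 0.5- and 1-month rows approximate the real-time phase. The later rows show what an unlimited delay could do in the prospective phase.

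**6. Check of the remedy.** If each patient is classed from the diagnostic sample whether or not still alive, or if both groups start at a common landmark, the artefact in this no-effect model is 0.

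**The case against.** The strongest reply is that the article never says a change must happen during life. WGTS mostly uses surplus DNA and RNA from the diagnostic sample, so an early death does not stop sequencing, and each patient gets a study report with the potential impact on risk stratification. If the comparison is built from that record, early deaths are included and the bias vanishes. This stands as a possibility, but the outcome sentence does not say that the record defines the groups.

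Several stronger inferences should be resisted:

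- A reader might infer that early deaths all fall on the SoC side. No section assigns patients who die before the report to any group, and deaths after the report can occur on both sides.
- A reader might infer that the delay is unlimited for everyone. The real-time phase has fixed report times. The day-29 sample matters only where it is the germline source in adult ALL; a skin biopsy is listed first.
- A reader might infer that the net comparison must favour WGTS. WGTS can move patients to a better or a worse risk group, so case mix may mask or reverse the difference. Only the immortal-time component has a known direction.
- A reader might infer that the cost-effectiveness ratio is inflated by these amounts. The model's value is said to be driven by the proportion with changed or changeable management, and how this outcome contrast enters the model is not stated.

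The contrast will also be imprecise. With 16% of 450 = 72 reclassified and survival of 50%, the standard error of the difference is √[0.25 × (1/72 + 1/378)] = 6.4 points, so artefacts of 2.6 or 5.6 points lie within one standard error. That limits how visible the bias would be. It does not remove it from the point estimate.

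**Conclusion.** The concern holds in conditional form. If reclassified means that WGTS actually changed the risk group, the definition excludes deaths before the report and raises that group's apparent survival. The effect matters mainly in the prospective phase. Its size rests on assumed early mortality and delay: +2.6 to +12.5 points at 2-year survival of 50% with 5% to 20% dying before the report, and less with the fixed report times of the real-time phase. It is zero if groups are formed from the study report regardless of survival. The primary endpoints are untouched, and the affected contrast belongs to a secondary health-economic endpoint. It should be corrected before outcome data are analysed, because the wording leaves the biased reading open and the remedy uses information already planned.

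**What to change.** State in the health-economic analysis plan that every sequenced patient, including those who died before the report, is classed twice from the WGTS study report: by SoC risk group and by SoC plus WGTS risk group. Follow-up starts at diagnosis. The classification rule, including how unverified variants and missing germline samples are handled, should not depend on whether the patient was still alive.

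If changes that were acted on are also analysed, use one of two forms:

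- a landmark, comparing only patients alive and under follow-up at the same time since diagnosis; or
- reclassification as a time-dependent variable, so that time before the report counts as not reclassified.

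Both need the date of the WGTS report. The listed contents of the study report include turnaround time for the real-time phase only, so the sponsor should confirm that the date is recorded in the prospective phase too.

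**Cost.** The main change is a few sentences in the analysis plan and no new data. The second analysis needs one date per patient. The landmark form drops deaths before the landmark and loses some precision.
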